## Abstract

**Background:**

Rapamycin is an inhibitor of the mechanistic target of rapamycin (mTOR) protein kinase, and preclinical data demonstrate that it is a promising candidate for a general gero- and neuroprotective treatment in humans. Results from mouse models of Alzheimer’s disease have shown beneficial effects of rapamycin, including preventing or reversing cognitive deficits, reducing amyloid oligomers and tauopathies and normalizing synaptic plasticity and cerebral glucose uptake. The “Evaluating Rapamycin Treatment in Alzheimer’s Disease using Positron Emission Tomography” (ERAP) trial aims to test if these results translate to humans through evaluating the change in cerebral glucose uptake following six months of rapamycin treatment in participants with early-stage Alzheimer’s disease.

**Methods:**

ERAP is a six-month-long, single-arm, open-label, phase IIa biomarker-driven study evaluating if the drug rapamycin can be repurposed to treat Alzheimer’s disease. Fifteen patients will be included and treated with a weekly dose of 7 mg rapamycin for six months. The primary endpoint will be change in cerebral glucose uptake, measured using [^18^F]FDG positron emission tomography. Secondary endpoints include changes in cognitive measures, markers in cerebrospinal fluid as well as cerebral blood flow measured using magnetic resonance imaging. As exploratory outcomes, the study will assess change in multiple age-related pathological processes, such as periodontal inflammation, retinal degeneration, bone mineral density loss, atherosclerosis and decreased cardiac function.

**Discussion:**

The ERAP study is a clinical trial using in vivo imaging biomarkers to assess the repurposing of rapamycin for the treatment of Alzheimer’s disease. If successful, the study would provide a strong rationale for large-scale evaluation of mTOR-inhibitors as a potential disease-modifying treatment in Alzheimer’s disease.

**Trial registration:**

ClinicalTrials.gov ID NCT06022068, date of registration 2023–08-30.

**Supplementary Information:**

The online version contains supplementary material available at 10.1186/s12883-024-03596-1.

## Background

For many decades, the “amyloid hypothesis” has been the dominant scientific lead in understanding and treating Alzheimer's disease (AD). Clinical trials that directly target amyloid plaques (such as amyloid antibodies) have however resulted in mixed success [1]. Only recently have two amyloid antibodies been given accelerated approval by the FDA. The drugs are prohibitively priced and questions about their efficacy and safety profile remain [2]. It is therefore crucial to explore new scientific approaches to find an efficient disease-modifying intervention. One such approach is to focus on the single largest risk factor for AD: advancing age.

It is estimated that the risk of developing AD doubles every five years over the age of 65 [3], and the risk of death from AD increases by about 700 times between the ages of 55 and 85 [4]. Within the field of geroscience, which focuses on the biology of aging, an increasing number of interventions have been shown to enhance the lifespan of model organisms and slow down or prevent age-related pathology [5]. One promising approach to understand and treat age-related diseases like AD is to study the effects of such interventions; defined as “geroprotective compounds”, in humans [6]. Pre-clinical data suggest that the drug rapamycin is a promising candidate for this purpose [6, 7].

Rapamycin, also known as *sirolimus*, is an immunosuppressive drug which has been in clinical use for more than two decades. In mice, treatment with rapamycin increases average lifespan by 10 to 15% [8]. The drug has also been shown to increase healthspan in model organisms by delaying the onset of age-related diseases [9]. For example, preclinical data support a beneficial effect of rapamycin (or its analogues) on periodontitis [10], retinal pathologies [11, 12], atherosclerosis [13, 14]; cardiac dysfunction [15, 16], and bone mass loss [17, 18]. Such diseases are commonly manifested with increasing age and are considered frequent comorbidities to AD [19–31].

There is a large body of preclinical data suggesting that repurposing rapamycin to treat AD could be effective [6, 7]. In several independent mice models of AD, rapamycin has been shown to prevent and reverse cognitive deficits [32, 33], reduce amyloid oligomers and tauopathies [34, 35], normalize synaptic plasticity [36], cerebral glucose uptake and [33] vascular cognitive impairment [37]. Additionally, in transgenic rodent models of AD, rapamycin has demonstrated neuroprotective effects by restoring blood–brain barrier function [32] and improving neurovascular coupling [38].

Despite promising preclinical data supporting rapamycin as an effective agent in alleviating or reversing AD pathology, no large-scale human clinical studies have been initiated. Currently, only one phase II trial is ongoing (ClinicalTrials.gov ID: NCT04629495).

Conducting randomized controlled trials (RCTs) with symptom ratings (such as cognitive ability) as endpoints is challenging due to the need for large sample sizes and high costs. An alternative approach is to assess the impact of candidate interventions on AD biomarkers before initiating such large-scale RCTs. By focusing on well-established and precise biomarkers of the disease rather than symptom ratings, evidence of slowing or even reversal of pathology can be obtained with much smaller sample sizes [39, 40].

The purpose of the study “Evaluating rapamycin treatment in Alzheimer’s disease using positron emission tomography” (ERAP) is to assess the effect of rapamycin in treating early-stage AD. This will be done by measuring changes in biomarkers using in vivo imaging modalities, such as positron emission tomography (PET) and magnetic resonance imaging (MRI), as well as biomarker changes in cerebrospinal fluid (CSF). We will test the hypothesis that rapamycin can reverse AD-associated brain pathologies, resulting primarily in an increase in neuronal glucose metabolism, and secondarily in an improved cerebral blood flow and a decrease in tau and amyloid protein aggregates in the CSF. We will also record the occurrence of adverse events and investigate pharmacokinetic properties of the drug. Further, we aim to explore the effect of rapamycin on other age-related pathologies in the body using different imaging techniques to assess changes in i) periodontal inflammation, ii) retinal structures, iii) bone mineral density, iv) atherosclerosis, as well as v) cardiac function. The results from this phase IIa trial will be used to inform on the feasibility of conducting a larger controlled trial in the future.

## Methods

### Study design

ERAP is a single-centre, open-label, one-arm, phase IIa intervention study. Fifteen patients diagnosed with early-stage AD will be recruited from the Karolinska University Hospital, Medical Unit Aging Memory clinic, located in Solna, Stockholm, Sweden. The unit is a specialized outpatient clinic that examines individuals referred by general practitioners in primary and occupational health care in the northern catchment of Stockholm, as well as individuals younger than 70 years in the entire Stockholm region [41].

Following baseline measurements, all participants will receive a weekly oral dose of 7 mg rapamycin (Tablet Rapamune®) for a duration of six months. Throughout the study, participants will be continuously monitored for safety and adverse events. By the end of the treatment period, follow-up measurements will be conducted. Figure 1 presents a schematic overview of the study timeline for each participant.

**Fig. 1 Fig1:**
[figure not shown]
Study timeline for each participant

### Participants

The study will enrol patients with early-stage AD, defined as fulfilling criteria for Alzheimer’s clinical syndrome, with either mild cognitive impairment (MCI) or mild dementia of the Alzheimer's type, according to the NIA-AA (National Institute of Aging-Alzheimer's Association) 2018 criteria [42] (see Table 1 for specific study eligibility criteria).

**Table 1 Tab1:** Eligibility criteria

Study eligibility criteria
*Inclusion criteria* 1. Age: 55–80 years. 2. Has an available “study partner” who can accompany the participant to planned visits. 3. Has a clinical diagnosis of MCI (mild cognitive impairment) or dementia of the Alzheimer's type, and: ◦ At inclusion, the participant meets the criteria for “Alzheimer’s clinical syndrome”, MCI, or mild dementia of the Alzheimer's type, according to the NIA-AA (National Institute of Aging-Alzheimer's Association) 2018 criteria [42]. ◦ At inclusion, the participant is amyloid positive, established with either amyloid PET imaging, or a CSF beta amyloid 1–42 assay, or a CSF beta amyloid 1–42/ beta amyloid 1–40 assay. 3.1 For participants with dementia, the disease should be in an early stage, operationalized as: ◦ Having stage 4 mild dementia or lower, according to the NIA-AA 2018 clinical staging criteria [42]. ◦ Having a clinical Dementia Rating Scale (CDR) global score of 1 or lower. ◦ Having a Montreal Cognitive Assessment (MoCA) score of ≥ 18 or a Rey Auditory Verbal Learning Test (RAVLT) > 4 words after 30 min. 3.2 For participants with a diagnosis of MCI, a cognitive deficit with > -1SD in at least one of the following cognitive tests: Wechsler Adult Intelligence Scale subtest to assess processing speed/attention, Rey Auditory Verbal Learning Test (learning and delayed recall), or Rey Complex Figure Test. 4. Is proficient in the Swedish language. 5. Has a normal or clinically acceptable medical history, physical examination, and vital signs. 6. For female participants, the participant has no childbearing potential, meaning that she is surgically sterile or post-menopausal, or has a negative pregnancy test following a menstrual period AND uses an acceptable effective contraceptive measure, which must be continued for at least 12 weeks after stopping the study drug.
*Exclusion criteria* 1. Has a history of any major disease that may interfere with safe engagement in the intervention (especially severe liver or kidney disease, or uncontrolled diabetes). 2. Has a history of a major neurological disorder, central nervous system infarct, infection or focal lesions of clinical significance on MRI scans. 3. There is evidence of a clinically relevant or unstable psychiatric disorder, based on Diagnostic and Statistical Manual of Mental Disorders (DSM-5) criteria, including schizophrenia or other psychotic disorder, or bipolar disorder. 4. Fulfills any contraindication for the use of rapamycin, including (but not restricted to): ◦ Current or planned medication with a strong inhibitor of CYP3A4 or P-gp. ◦ Current or planned medication with a strong inducer of CYP3A4 or P-gp. ◦ Other current medications with known serious interaction risks with rapamycin. ◦ Known allergy or hypersensitivity to rapamycin. 5. Has significant obesity, as per the investigator's judgement. 6. Has untreated hyperlipidemia that is clinically significant, as per the investigator's judgement. 7. Has undergone treatment with immunosuppressive medications within the last 90 days, or treatment with chemotherapeutic agents for malignancy within the last 3 years. 8. Has had major surgery within 3 months prior to the planned start of rapamycin treatment, or has major surgery planned during the trial period. 9. Has used experimental medications for AD or any other investigational medication or device within the last 60 days of inclusion. ◦ Participants who have been involved in a monoclonal antibody study are excluded unless it is known that they were receiving placebo in that trial.

### Study drug

Rapamycin was approved in 1999 in the USA and in 2001 in Europe as an immunosuppressive drug to prevent organ rejection in renal transplantation [43]. The drug and structurally analogous compounds (known as “rapalogs”), such as everolimus, have been approved for the treatment of several solid tumours [44, 45], and is currently the only pharmacological option when treating tuberous sclerosis complex (TSC) [46]. Rapamycin exerts its effect by inhibiting the intracellular protein kinase mTOR, which stands for “mechanistic target of rapamycin”. mTOR has been shown to be central in the regulation of several important functions in mammalian cells, such as cell growth and proliferation, protein synthesis, and autophagy [47].

The bioavailability of orally administered rapamycin is low (approximately 15%) and highly variable (SD = 9%). The drug is metabolized in the liver, primarily by CYP3A4, with a terminal half-life of 62 h, though also here with large interindividual variability (SD = 16 h) [48].

#### Adverse events, mitigation strategies and dosing

The side effect profile of rapamycin is well known from a large number of clinical trials and from long clinical use. The treatment is generally well tolerated, but common side effects, as described in the product information [43] are; stomatitis, diarrhea, and nausea. Changes in clinical laboratory values observed during rapamycin treatment include increased blood levels of cholesterol and triglycerides, and bone marrow depression manifesting as thrombocytopenia and anemia. The incidence of bacterial infections has been reported as increased in cancer patients treated with rapamycin, along with reports of cases of non-infectious pneumonitis [44].

Notably, the data on side effects is based on the use of rapamycin following organ transplantation, where the drug is commonly used together with other immunosuppressants. In the ERAP trial, we plan to deviate from the standard dosing of rapamycin in two ways. Typically, when used as an immunosuppressant, rapamycin is administered orally at a daily dose of 2 mg or above [43]. We will instead administer an overall lower dose but in an intermittent fashion; a weekly oral dose of 7 mg. This change is aimed at reducing the risk of adverse events. The rationale behind this is that positive effects of rapamycin are hypothesized to be caused by inhibition of the mTOR1 complex, while many of the side effects are hypothesized to be due to inhibition of the mTOR2 complex. While mTOR1 is sensitive to acute dosing treatment, mTOR2 requires sustained exposure of the drug to be effectively inhibited [45].

Patients will be monitored for side effects during the study, including the collection of blood samples at follow-up visits (see Table 2). These samples will be analysed for standard clinical measures, including parameters known to be affected by rapamycin: complete blood count with differential and platelet count, sodium, potassium, chloride, albumin, creatinine, bilirubin, alkaline phosphatase, alanine aminotransferase, aspartate aminotransferase, gamma-glutamyl transferase, glucose, cholesterol, triglycerides, calcium, phosphorus, and creatine phosphokinase.

**Table 2 Tab2:** Visits, follow-ups and their corresponding assessments/examinations

Procedure	Screening and inclusion	Baseline imaging	Phone follow-up 1	Clinical follow-up 1	Phone follow-up 2	Clinical follow-up 2	Follow-up imaging	Clinical follow-up 3
		-42 to 1 day(s) before first dose	1–3 days after first dose	5–14 days after first dose	23–56 days after first dose (± 14 days)	71–105 days after first dose (± 14 days)	-14 to 27 days after last dose	≤ 28 days after last dose
Check inclusion/exclusion criteria	√	√	√	√	√	√	√	√
Medical history/concomitant medications	√		√	√	√	√		√
Physical and Neurological Examination	√			√		√		√
Instructions for taking the study drug	√	√						
Retinal OCT^a^		√					√	
[^18^F]FDG PET and qCT^a^		√					√	
Head/brain MRI^a^		√					√	
Cardiovascular MRI^a^		√					√	
Start treatment with study drug^c^		√						
Blood collection ^d^				√		√^b^		√
Lumbar puncture^d^	√							√
Cognitive testing^d^	√							√
Adverse Events (AE & SAE)			√	√	√	√		√
Study end								√

^a^For the PET, MRI, and the OCT examinations, the order is interchangeable

^b^Pharmacokinetic testing will consist of a total of 4 blood samples per participant. Blood samples will be collected for determining the concentration of rapamycin as follows: within 1 h prior to administration of rapamycin, at 1 and 3 (± 30 min) hours post administration of rapamycin, and 48 h post administration

^c^ The first weekly dose of rapamycin will be taken on a weekday, after completing the baseline measurements. The treatment will last for 26 weeks (182 days)

^d^In the event that patients are included where the most recent lumbar puncture and/or blood tests and/or cognitive testing are > 9 months old, one additional visit will be planned for new measurements to function as baseline values

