### Visits and data collection

Table 2 and Supplementary Information (Additional file 1) outline the study visits, follow-ups, and corresponding assessments. In brief, participants will be invited to a first screening visit accompanied by a study partner. During this visit, the study will be explained in detail and written informed consent will be obtained. Basic clinical and demographic information will be collected, and the study eligibility criteria will be assessed (see Table 1).

Before initiating the study treatment, the following baseline examinations will be performed: [^18^F]Fluorodeoxyglucose ([^18^F]FDG) PET/CT imaging, brain and head MR imaging, cardiological MR imaging, retinal optical coherence tomography, lumbar puncture for collection of a CSF sample, as well as neuropsychological testing and physical aptitude. At the end of the treatment period, the same set of follow-up examinations will be conducted.

 Throughout the treatment period, participants will attend three clinical follow-up visits. At every visit, information on side effects will be collected. During the second clinical follow-up, blood samples will be collected at four time points over 48 h to assess the drug’s pharmacokinetic properties (just before and 1,3, and 48 h after intake of the weekly dose). At the third clinical follow-up visit, which will occur after the final dose of the study drug, neuropsychological cognitive tests will be performed and a CSF sample will be collected. Additionally, participants will have at least two scheduled phone calls during the study to assess adverse events or changes in concomitant medications/supplements.

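### Table 2 lists no adverse-event enquiry, medication review or safety blood test between clinical follow-up 2 and the post-treatment visit: a gap of at least 56 days, and of 132 to 153 days at the edges of the windows

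*Protocol article*

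**What the plan says.** Three parts of the protocol article bear on this.

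- **Table 2.** The row "Adverse Events (AE & SAE") is marked at five contacts: phone follow-ups 1 and 2 and clinical follow-ups 1, 2 and 3. Concomitant medication is marked at screening and at the same five. Blood collection is marked at clinical follow-ups 1, 2 and 3 only. Clinical follow-up 2 falls at "71–105 days after first dose (± 14 days") and clinical follow-up 3 at "≤ 28 days after last dose". Follow-up imaging lies between these two columns. It is marked for the eligibility check and the scans, but not for adverse events, medication or blood. A footnote adds: "The treatment will last for 26 weeks (182 days").
- **Study design.** "Throughout the study, participants will be continuously monitored for safety and adverse events".
- **Visits and data collection.** Three clinical follow-up visits are placed across the treatment period, and then: "At every visit, information on side effects will be collected". The same section puts the third of these visits after the final dose. Two phone calls are set as a minimum.

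Table 3 makes the incidence of adverse events, together with laboratory data and vital signs, the endpoint for the safety objective.

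**The concern.** Four of the five adverse-event contacts, and two of the three safety blood samples, come no later than clinical follow-up 2. The rest of the dosing period has no listed safety contact until a visit after the last dose. A reader of the Study design section would expect otherwise.

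What is at stake is how well a stated secondary endpoint is ascertained. Participants are selected for cognitive impairment. At clinical follow-up 3 they would be asked about mild, short-lived events, such as the stomatitis, diarrhoea and nausea that the article lists as common, over a period of weeks to months. A transient laboratory change in that period would not be measured at all. The article says that its side-effect data come from transplant use and that the trial is meant to inform a larger one, so the late-treatment safety record matters.

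**Working it through.** **Inputs**

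- Clinical follow-up 2: day 71 to 105, with 14 days either way (Table 2).
- Clinical follow-up 3: 0 to 28 days after the last dose (Table 2; the text places it after the final dose).
- Treatment duration: 26 weeks. Check: 26 × 7 = 182 days, as printed.
- Dosing: "all participants will receive a weekly oral dose of 7 mg rapamycin" (Study design). The day of the last dose is not given. Assumption: day 175 (26th weekly dose with the first on day 0, 25 × 7 = 175) up to day 182.

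**Two readings of the window**

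- Added: 71 − 14 = day 57 to 105 + 14 = day 119.
- Inside: the printed range already contains the 14 days, so day 71 to 105. This is plausible: 71 + 14 = 85 and 105 − 14 = 91 would be a target of days 85 to 91. Likewise 23 + 14 = 37 and 56 − 14 = 42 for phone follow-up 2.

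**Formulas**

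- Longest gap = (last dose + 28) − earliest clinical follow-up 2.
- Longest on-treatment part = last dose − earliest clinical follow-up 2.
- Shortest gap = last dose − latest clinical follow-up 2.

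| Reading | Last dose | Longest gap | Longest on-treatment part | Shortest gap |
|---|---|---|---|---|
| Added | day 175 | 203 − 57 = 146 | 175 − 57 = 118 (64.8% of 182) | 175 − 119 = 56 |
| Added | day 182 | 210 − 57 = 153 | 182 − 57 = 125 (68.7%) | 182 − 119 = 63 |
| Inside | day 175 | 203 − 71 = 132 | 175 − 71 = 104 (57.1%) | 175 − 105 = 70 |
| Inside | day 182 | 210 − 71 = 139 | 182 − 71 = 111 (61.0%) | 182 − 105 = 77 |

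Mid-window is (71 + 105) / 2 = day 88 on either reading. From there the gap runs from 175 − 88 = 87 to 210 − 88 = 122 days.

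**Would a mark at the imaging visit close the gap?** Imaging opens 14 days before the last dose, on day 161 or 168. At its earliest it still leaves 161 − 71 = 90 to 168 − 57 = 111 days after the earliest clinical follow-up 2. It may also fall as late as 27 days after the last dose, close to clinical follow-up 3. So this mark alone is not enough.

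**Would moving phone follow-up 2 close it?** That would leave no adverse-event contact between clinical follow-up 1 (from day 5) and clinical follow-up 2: up to 105 − 5 = 100 days (inside) or 119 − 5 = 114 days (added). A call has to be added, not moved.

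**The case against.** The case on the other side is substantial, and much of it stands.

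- **The every-visit statement is not breached.** A reader might infer that Table 2 contradicts it. In its section the sentence follows directly on the three clinical visits, and all three are marked for adverse events. The article describes the imaging session separately. This stands.
- **Continuous monitoring can include unsolicited reports.** The Adverse events section commits to recording all events, and two calls is a floor. So this is a tension, not a strict contradiction. That stands, but neither statement puts a scheduled enquiry into the gap.
- **Additional file 1 is not shown.** The article refers to it for visits and safety detail, and it may list more contacts. That limits what can be said about trial conduct. It does not make the published table agree with the published text.
- **Undercounting is not shown.** A reader might infer that incidence will be biased low. Clinical follow-up 3 asks about events and can pick up earlier ones, and a study partner who can attend planned visits is an entry requirement. The article gives no event or recall rates. This stands, except that a study partner cannot supply a laboratory value that was never measured.
- **The imaging visit is not empty.** The eligibility check is marked there, and the criteria touch on interacting drugs and major disease. That is some contact, but it is neither an adverse-event enquiry nor a medication review.
- **Early-weighted contacts are a legitimate design choice.** Agreed. The point is the unlisted later period and the wording that does not match it.

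**Conclusion.** The point holds in a limited form. On any reading of the windows, Table 2 lists no adverse-event enquiry, concomitant-medication review or safety blood test for at least 56 to 77 days, up to the end of dosing. From mid-window the gap is 87 to 122 days. At most it is 132 to 139 days if the 14 days lies inside the printed range, or 146 to 153 days if it is added. The figures rest on the assumed last-dose day of 175 to 182.

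A reader might take about 150 days, or more than two-thirds of treatment, as the typical gap. The article does not support that. The figure needs the added reading, the earliest clinical follow-up 2 and the latest clinical follow-up 3, and it includes up to 28 days after the last dose. The on-treatment share is 57% to 69% of 182 days at the extreme, and smaller otherwise.

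The consequence is a plausible risk of under-ascertaining mild or transient events late in treatment; its size cannot be derived from the article. Separately, the double specification of the window is a drafting fault, and only two of the three clinical visits described as spanning the treatment period precede the final dose.

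**What to change.** 1. In Table 2, mark adverse events and concomitant medication at the existing follow-up imaging visit.
2. Add one adverse-event call between clinical follow-up 2 and the end of treatment, with the study partner taking part. The text already allows more than two calls. Keep phone follow-up 2 where it is.
3. Replace each range that carries an extra 14 days either way with one window that has a single earliest and a single latest day.
4. Reconcile the Study design statement, the Visits and data collection section and Table 2. This includes whether the listed blood monitoring matches the stated continuous monitoring, which is for the sponsor to settle; no clinical monitoring rule is proposed here.

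Cost: two marks in a table, one short call for each of 15 participants (15 calls) and slightly more adverse-event data entry. No new visit is needed.

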### Objectives and endpoints

Table 3 presents the study objectives along with their respective outcomes and endpoints.

**Table 3 Tab3:** Study objectives and endpoints

Primary objective	Primary endpoint
To evaluate the efficacy of rapamycin treatment in patients with early-stage Alzheimer’s disease	Change-from-baseline for: • [^18^F]FDG brain uptake, measured with PET
	Secondary endpoints
	Change-from-baseline for: • MoCA total score • CSF levels of amyloid beta, p-tau, and t-tau • Cerebral blood flow, measured with MRI using a non-invasive pseudo-continuous arterial spin-labeling sequence
	Exploratory endpoints
	• Physical performance: ◦ Timed 10 m walking test ◦ Timed 10 m dual-task test ◦ 30 s chair stand test ◦ Hand strength • Neuropsychological cognitive testing using: ◦ Rey Auditory Verbal Learning Test (learning and delayed recall) ◦ Rey–Osterrieth Complex Figure ◦ Hagman test ◦ Trail Making Test A + B ◦ Wechsler Adult Intelligence Scale, 4th edition coding subtest to assess processing speed/attention
Secondary objectives	
To evaluate pharmacokinetic properties of intermittent dosing of rapamycin	Whole blood measurements of rapamycin concentration: ◦ C_max_ ◦ C_trough_ ◦ Area under the curve
To evaluate the safety and tolerability of rapamycin when intermittently dosed against AD	Safety and tolerability as measured by incidence of AEs/SAEs; clinical laboratory test data; vital signs
Exploratory objectives	
To evaluate a general “geroprotective” effect of rapamycin treatment, by measuring changes in age-related tissue pathologies, such as: • Periodontal associated inflammation • Retinal degeneration • Atherosclerosis in large arteries • Heart function • Myocardial inflammation • Bone mineral density	Change-from-baseline for: • Periodontal oedema and bone remodeling, measured using MRI and CT • Thickness and thickness ratios of retinal nerve fiber layers in the macula and optic disc, measured using OCT • Pulse wave velocity in the aorta, measured using MRI • [^18^F]FDG uptake in atherosclerotic plaques in large arteries • Heart function (including, but not limited to: diastolic function, microvascular function, myocardial-volume and strain), measured with MRI • Bone mineral density in lumbar vertebrae, measured using qCT

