### Statistics

Based on the relatively low variability in long-term test–retest data of [^18^F]FDG in humans [55, 56], a sample size of *N* = 15 is estimated to be sufficient to detect a 5% change in cerebral grey matter metabolic rate at 80% power with a significance level of 0.05. Such a hypothesized effect size is considered feasible given previous trials of AD using [^18^F]FDG as an outcome measure [57, 58].

The change in estimated metabolic rate of grey matter [^18^F]FDG between baseline and follow-up imaging will be assessed using a paired t-test. Additionally, grey matter differences in standardized uptake value ratios, using the cerebellum as a pseudo-reference region (denominator), will be evaluated as a complementary outcome measure of [^18^F]FDG uptake. The level of significance will be set at 0.05.

Paired t-tests will also be used to assess differences between baseline and end-of-study secondary outcome measures. We will also explore if pharmacokinetic parameters are correlated with 1) each other, 2) side effect burden, 3) treatment effect using linear models.

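### Baseline MoCA, neuropsychological and CSF values may be up to 9 months old, so their six-month change can be more than half pre-treatment time

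*Protocol article*

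**What the plan says.** Table 2 of the protocol article places lumbar puncture and cognitive testing at screening and inclusion, with no day window relative to first dose, and again at clinical follow-up 3. Footnote d is attached to the blood, lumbar puncture and cognitive testing rows. It provides for a repeat, to supply the baseline, only in patients "where the most recent lumbar puncture and/or blood tests and/or cognitive testing are > 9 months old, one additional visit will be planned". It does not say outright that younger values serve as baseline, but no other reading gives the footnote a purpose.

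Imaging is held to a tighter rule: the baseline imaging column is limited to "42 to 1 day(s) before first dose". Treatment lasts 26 weeks (182 days), and clinical follow-up 3 takes place "≤ 28 days after last dose".

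Table 3 lists MoCA, "CSF levels of amyloid beta, p-tau, and t-tau" and cerebral blood flow as secondary change-from-baseline endpoints, with the neuropsychological battery as exploratory. Under Statistics: "Paired t-tests will also be used to assess differences between baseline and end-of-study secondary outcome measures". The article mentions no adjustment for the age of the baseline value. The trial has one arm.

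**The concern.** In a single-arm trial the pre/post difference is the only evidence on efficacy. It can be read as change under treatment only if the first measurement is taken close to the first dose. Early-stage Alzheimer's disease progresses, so a baseline taken months earlier adds untreated decline to the measured change. That amount varies with how long ago each patient was worked up at the clinic, so it shifts the mean and also adds spread.

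The hypothesis is improvement. For MoCA, decline before the first dose works against a true gain and can make a stable patient look worse. The trial is meant to inform a decision on a larger controlled study, and MoCA and CSF are two of its three groups of secondary efficacy endpoints.

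**Working it through.** **The plan's own figure.** The article gives no calculation for these endpoints. Its only sample-size statement (N = 15, 5% change, 80% power, level 0.05) concerns FDG. A two-sided paired t-test with n = 15 has 80% power at a standardised change of 0.778, so the statement implies an SD of change of about 5/0.778 = 6.4%. No SD is stated, so N can be neither confirmed nor refuted. Nothing below depends on it.

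**Inputs from Table 2 and its footnotes**
- Oldest baseline accepted: 9 months = 9 × 30.44 = 274 days.
- Treatment: 182 days.
- Final CSF and cognitive tests: up to 28 days after last dose (end of treatment taken as day 182).
- Imaging window: at most 42 days before first dose.

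**Length of the paired interval.** Interval = pre-dose gap + 182 + delay to follow-up. Pre-dose share = gap / interval.

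| Case | Interval (days) | Months | Pre-dose share |
|---|---|---|---|
| 9 months old, no delay | 274 + 182 = 456 | 15.0 | 274/456 = 60% |
| 9 months old, 28-day delay | 274 + 182 + 28 = 484 | 15.9 | 274/484 = 57% |
| 42-day window, no delay | 42 + 182 = 224 | 7.4 | 42/224 = 19% |
| 42-day window, 28-day delay | 42 + 182 + 28 = 252 | 8.3 | 42/252 = 17% |

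Footnote d does not say at what point the 9 months is counted. If it is counted at inclusion, and if the first dose follows 42 days later (an assumption; 42 days is the imaging window, not a stated inclusion-to-dose gap), the maximum is 274 + 42 + 182 + 28 = 526 days (17.3 months), of which 316/526 = 60% is pre-dose.

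**Illustration for MoCA.** None of these inputs is in the document: untreated decline of 1 to 2 points per year, SD of change 2 to 3 points, n = 15, two-sided 0.05.

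Bias = rate × gap. At an average gap of 4.5 months (0.375 years) this is 1 × 0.375 ≈ 0.4 to 2 × 0.375 ≈ 0.8 points. If every patient had the full 9 months, it would be 0.75 to 1.5 points.

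The probability of a significant result comes from the noncentral t with 14 df and noncentrality (mean change / SD) × √15. For a MoCA that is truly stable on treatment:

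| Bias | SD 2 | SD 2.5 | SD 3 |
|---|---|---|---|
| 0.4 | 11% | 9% | 8% |
| 0.8 | 30% | 21% | 16% |

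The nominal rate is 5%, and nearly all of the excess is apparent worsening.

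For a true 2-point gain, the expected measured gain is 2 − 0.4 = 1.6 or 2 − 0.8 = 1.2. Power:

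| Expected measured gain | SD 2 | SD 2.5 | SD 3 |
|---|---|---|---|
| 2.0 | 95% | 82% | 67% |
| 1.6 | 82% | 64% | 49% |
| 1.2 | 58% | 41% | 30% |

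No comparable figure is offered for the CSF markers, because the document gives no rate of change or variability for them.

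**The case against.** The strongest defence is that this is a small exploratory phase IIa trial whose Limitations section admits that there is no control group, and that reusing a recent clinical lumbar puncture spares patients a second one. Both points are fair, and the second is a good reason not to demand a fresh CSF baseline. Neither covers MoCA and the cognitive tests, which are easily repeated. The admission concerns the missing comparator, not baseline intervals that are unequal and partly untreated. An analysis plan could adjust for the interval, but it cannot recover a measurement that was never taken.

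Several stronger readings are tempting, and the document does not support them:

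- *All secondary endpoints are affected.* Cerebral blood flow is measured by MRI within the imaging window, as is the primary FDG endpoint.
- *Blood values are biased endpoints.* Footnote d covers blood, but Table 3 uses it only as safety laboratory data, where an old value is a weak reference. Table 2 ticks no pre-dose blood draw, but visit detail is deferred to a supplement that is not shown.
- *Footnote d contradicts Visits and data collection.* That section says "Before initiating the study treatment, the following baseline examinations will be performed" and sets no time limit. A 9-month-old value still precedes treatment.
- *Regression to the mean adds to the bias.* Some of these measures are also entry criteria, but they select in different directions: a minimum MoCA or a RAVLT alternative for dementia, a deficit for MCI, and amyloid positivity. The net effect is not shown.
- *Stale baselines could create false efficacy.* For MoCA, untreated decline points the other way.

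**Conclusion.** The point holds for MoCA, the CSF markers and the exploratory neuropsychological tests. As footnote d stands, a paired difference presented as the effect of six months' treatment can cover 15.0 to 15.9 months, with 57 to 60% of it before the first dose. The 526-day figure needs the added assumption about the inclusion-to-dose gap.

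These are maxima. The distribution of actual gaps is not given, so the real bias may be much smaller. The 8 to 30% false-signal rates and the fall in power from 82% to 64% or 41% (SD 2.5) are illustrations for MoCA only and rest on assumed decline rates and SDs. For MoCA, the likely error is a missed benefit or an apparent harm.

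Severity: should-fix. Interpretation of secondary and exploratory endpoints is weakened; the primary endpoint is untouched.

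**What to change.** Amend footnote d so that MoCA and the cognitive battery are measured for every participant within the existing 42-day pre-dose window, and use those values as baseline. A participant whose screening tests already fall in that window needs no repeat. The cost is a somewhat longer baseline visit. A baseline safety blood sample can be taken at the same visit if the full protocol does not already provide one.

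For CSF, add no punctures. Record the interval from lumbar puncture to first dose, keep all participants in the main analysis, and prespecify a sensitivity analysis that either adjusts for the interval or restricts to recent punctures. With 15 participants a restricted set could be very small, so it should not be the main analysis, and the interval adjustment will be imprecise. Report the result as change since the last pre-treatment sample, not as a six-month change. The cost is one recorded date per participant and one extra analysis.
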